When shallow tubewells replaced highly contaminated surface water as the primary source of drinking water in Bangladesh in the late 20th century, contemporary studies demonstrated no reduction in diarrheal disease with this improvement in water source (Levine et al., 1976, Curlin et al., 1977, Sommer and Woodward, 1972, Khan et al., 1978, Briscoe, 1978). Some observers have argued that this lack of reduction in diarrhea following introduction of tubewells is likely a result of continued exposure to enteric pathogens from other sources (Levine et al., 1976, Briscoe, 1978). The lack of health improvements in transitioning to tubewells is consistent with the lack of significant health gains observed in intervention studies focusing on water quality improvements at the source (Fewtrell et al., 2005). Thus, one hypothesis to explain the failure of shallow tube wells to prevent diarrhea in Bangladesh, is that the resulting tubewell water remains too contaminated with enteric pathogens. Recent studies, including studies conducted by this research group, confirm that up to 40% of tubewells at any one time in various regions of Bangladesh are contaminated with thermotolerant coliforms or *Escherichia coli* (Hoque, 1999, Islam et al., 2001, Luby et al., 2006a, Hoque et al., 2006). However, the level of contamination is generally low. Among 207 tubewell water samples collected from 3 flood prone districts in Bangladesh in 2005, 29% were contaminated with thermotolerant coliforms (median 5 colony forming units/100ml, n=60), and 13% with *E. coli* (median 5 colony forming units/100ml, n=27) (Luby et al., 2008). The World Health Organization guidelines define safe drinking water as water that has less than 1 colony forming unit of *E. coli* per 100ml, and it is unclear if the level of contamination typically observed in tubewells in Bangladesh has a substantial impact on health. An alternative hypothesis to explain the failure of tubewells in reducing diarrhea is that even when relatively clean source water is available, contamination during collection, storage and handling may again put children at risk of diarrhea (Trevett et al., 2004),

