At each visit, we will also collect information on user compliance with the interventions by asking about type and timing of water treatment practices, counting the number of remaining tablets and inspecting the water storage facilities, as well as asking participants when and how they cleaned the storage container. We will also collect water samples from the tubewell and storage container in households to assess the microbial quality of the water, explore the extent of contamination at the source versus in the home and gauge the effectiveness of the interventions in preventing contamination. We will perform H2S testing in half of study households and total coliform/E.coli testing with membrane filtration for a subset of 150 households (50 from each study arm). Moreover, for each household in the Aquatabs group, we will analyze stored water samples for residual chlorine concentration to monitor compliance with the intervention.

**Laboratory Testing:** Water samples will be placed on ice and transported to the Fulbaria field office where the appropriate tests will be conducted by the field microbiologists. All testing will be performed promptly upon transporting the samples to the field office. The hydrogen sulfide (H2S) test is a simple low-cost test (Sobsey and Pfaender, 2003). Twenty ml of water will be added in H2S bottle and incubated at room temperature for 24-48 hours. If the colour of the water changes to black, it will indicate that the water is contaminated with coliform which will indicate that the water is unfit for human consumption. For membrane filtration, collected water samples will be quantitatively tested for total coliforms and E. coli using the DelAgua kit with MI Broth (Whatman Inc, New Jersey, USA). For residual chlorine testing, we will use the n,n-diethyl-p-phenylenediamine (DPD) colorimetric method which is part of the DelAgua kit.

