We will assess the magnitude of the differences in longitudinal prevalence by group by calculating a risk ratio between the groups. We will evaluate if risk ratios differ from 1.0 at traditional testing levels (*P*=0.05) using robust standard errors that account for repeated observations within children (Zeger and Liang 1986). We will repeat the calculations using the longitudinal prevalence of diarrhea among children under the age of five as the outcome measure to allow us to compare our results to other findings from the literature that focus on children under five.

Secondary outcomes will include the proportion of households by group that have contaminated water as measured by H2S testing and by quantitative evaluation of total coliforms and *E. coli.* We will assess the proportion of samples within each group that have no evidence of contamination. We will compare whether these proportions are different than would be expected by chance using chi square when there are no repeated samples and using general estimated equations when repeated samples are analyzed from the same household.

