The risks to study participants are few. Chlorine treatment of drinking water has been used for over a century and is widely recognized as a safe and appropriate way to treat drinking water. The specific chemical used for water treatment in this study, sodium dichloroisocyanurate, has been reviewed by the World Health Organization and judged to be safe (Clasen and Edmondson, 2006).

The control group will receive no water treatment during the study period, but will continue to be followed while they use their standard water collection habits and storage practices. This group risks being exposed to significant waterborne pathogens without treatment. If, over the course of the study, we encounter households in this group whose drinking water does not meet the WHO criteria for low risk (less than 10 CFU of thermotolerant coliforms per 100 mL), these households will be notified of their water quality results, informed about locally available water treatment methods and encouraged to use them. These include liquid bleach, bleaching powder and halotablets, as well as boiling. Moreover, this group is not being exposed to any increased risk by participating in the study. Indeed, their water collection and storage practices are the standard practices of tens of millions of Bangladesh households every day. We do not know if this low-level exposure to fecally contaminated drinking water leads to significant household diarrhea. Many commentators argue that low levels of contamination are not a significant health risk (Moe et al., 1991). The only way that we can learn whether increased efforts to improve the microbiological quality of drinking water will reduce diarrhea is by evaluating the intervention. This evaluation requires a non-intervention group for comparison.

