## Minor changes made to this protocol before study implementation:

1. Random subset of households in randomly selected villages (instead of systematic subset of households in villages close to the field office) to achieve representative random sample.
2. 180 households (60 from each study arm) tested for *E. coli* and total coliforms instead of 150 households (50 from each study arm) to achieve testing in 10% of study households.
3. MI Agar (Becton, Dickinson and Company, Maryland, USA) to enumerate *E. coli* and total coliforms instead of MI Broth (Whatman Inc, New Jersey, USA).
4. Digital colorimeter (Hach, Colorado, USA) to measure free chlorine residual instead of DelAgua kit to achieve increased precision.
5. Longitudinal prevalence in the protocol used to refer to period prevalence. Period prevalence measured to avoid inaccuracies associated with collecting diarrhea data for each day of the 7-day recall period.

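### E. coli and total coliform counts are compared between arms only as none versus any, which cannot show a fall in level when samples stay positive (minor)

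*Protocol*

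**What the plan says.** Under Laboratory Testing in Research Design and Methods, the protocol describes membrane filtration as quantitative for total coliforms and E. coli. The list of minor changes before implementation sets the subset: "180 households (60 from each study arm) tested for" E. coli and total coliforms. This replaces the 50 per arm in the main text. Follow-up sampling is meant, among other things, to compare how much contamination arises at the source and in the home.

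Data Analysis then fixes the use of these results. It begins "Secondary outcomes will include the proportion of households by group that have contaminated water as measured by H2S testing and by quantitative evaluation of total", where the sentence goes on to name the two organisms counted by filtration. The summary it then gives is "We will assess the proportion of samples within each group that have no evidence of contamination". The comparison of these proportions is to be made "using chi square when there are no repeated samples and using general estimated equations when repeated samples are analyzed from the same household". No comparison of counts is named, and the absence of contamination is not defined for each test or organism.

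Two other places bear on the cut-off. The Background cites a guideline under which safe water has under 1 CFU of E. coli per 100 ml. The Ethical Assurance section uses a graded threshold, "less than 10 CFU of thermotolerant coliforms per 100 mL", to decide when control households are told their results.

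**The concern.** The trial asks whether low-level contamination of drinking water matters, and the water results are the link between the interventions and diarrhea. If the diarrhea result is null, the reader will want to know how far contamination fell. Under the stated analysis, a household whose stored water falls from 200 to 8 CFU/100 ml is contaminated before and after. It has crossed the protocol's own 10 CFU line, yet it adds nothing to the comparison. A real fall in level could then be reported as no difference in contamination, although the counts that would show it are in hand.

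**Working it through.** **The plan's own figure.** 3 arms × 600 = 1,800 households, and 180/1,800 = 10%, as stated. The protocol gives no power, effect size or SD for the water outcomes, so every effect and spread below is an assumption.

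**Positivity in the documents (all tubewell water).** 29% for thermotolerant coliforms and 13% for E. coli among 207 samples (Background). For E. coli in very shallow wells, 9% in the dry season and 61% in the rainy season. No figure is given for stored water or for total coliforms.

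**Simulation 1: fall in level.** Counts are Poisson around lognormal household means with SD 0.9 log10, the geometric mean falls by 0.4 log10 (10^0.4 = 2.5-fold), and there are 60 households per arm at one visit, tested two-sided at 5%. Chi-square on none/any is set against a t-test on log10(count+1). Results move by a few points between runs.

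| Comparison arm positive | None/any | log10(count+1) |
|---|---|---|
| about 23–59% | 28–40% | 30–50% |
| 82% (geometric mean 5) | 34% | 60% |
| 93% (geometric mean 20) | 24% | 64% |
| 99% (geometric mean 100) | 7% | 66% |

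**Simulation 2: other kinds of effect**, again at 60 per arm and one visit.

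| Effect | None/any | t-test on log10 counts |
|---|---|---|
| Presence only, 13% to 5% positive | 0.34 | 0.27 |
| Presence only, 61% to 35% positive | 0.83 | 0.63 |
| 0.5 log10 fall (SD 0.8), 39% to 21% positive | 0.56 | 0.63 |
| 0.5 log10 fall (SD 0.8), 91% to 78% positive | 0.48 | 0.90 |
| 0.5 log10 fall (SD 0.8), 99% to 97% positive | 0.07 | 0.93 |
| 61% positive in both arms, median among positives 20 to 5 CFU | 0.05 | 0.68 |

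The none/any test is as good or better when the effect is on presence. It is far weaker when almost every sample is positive or when levels fall without clearing.

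**Repeat visits.** If the same households are sampled at all ten follow-ups, with an assumed ICC of 0.3, the effective number per arm is 60 × 10 / (1 + 9 × 0.3) = 600/3.7 ≈ 162. None/any power is then 0.74 for 13% to 5%, 0.89 for 91% to 78% and 0.33 for 99% to 97%. Where positivity does not change it stays near 0.05, however many visits are added, against 0.98 for log counts.

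**H2S volume.** The bottle takes 20 ml. The chance that V ml at c organisms per 100 ml holds at least one is 1 − exp(−cV/100). At c = 5 this is 1 − exp(−1) = 63% for 20 ml, and 1 − exp(−5) = 99% for 100 ml. The 100 ml is an assumption, since the filtered volume is not stated. A negative H2S result therefore does not mean the same as a zero count.

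**The case against.** The zero cut-off has a stated basis in the guideline for E. coli, and clearing water of contamination is a natural aim of chlorination. At the tubewell positivity reported, the none/any test loses little and can be the stronger one. Repeat sampling with GEE recovers part of the loss. The outcome is secondary, the list of secondary outcomes is open-ended, the counts are kept, and an analysis plan that is not shown may add a count model. All of this stands and limits the weight of the point. It does not remove it, because the protocol goes beyond silence: it names both the summary and the tests, and neither uses the counts.

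A reader might infer more than the text supports:

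- *That most of the power is lost in general.* This holds only near universal positivity or when levels fall without clearance.
- *That H2S and filtration results are mixed.* Data Analysis lists them as separate measures, Research Design and Methods gives them different household coverage, and nothing pools them.
- *That 5 CFU/100 ml is the typical level.* The figure "median 5 colony forming units/100ml, n=60" is the median among the 60 positives of 207 samples. With 71% negative, the overall median is zero.
- *That the H2S incubation ("Twenty ml of water will be added in H2S bottle and incubated at room temperature for 24-48 hours") distorts a dry/wet contrast.* The seasonal aims concern diarrhea, the planned water comparison is between concurrent randomized groups, and no seasonal H2S contrast is specified. Incubation at a controlled temperature is a laboratory preference.

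**Conclusion.** The concern holds in limited form and is minor. The only arm comparison stated for the counted organisms is a none/any proportion, so a fall in level among samples that stay positive goes unseen. The cost ranges from nothing, or a slight advantage, at 9–61% positive with an effect on presence, to power of 7–34% against 60–66% at 82–99% positive. The second range rests on the assumed SD of 0.9 log10, a 0.4 log10 fall and a single visit. Whether the trial's data lie there is not known from the documents. It is plausible for total coliforms, a broader group than E. coli, and for stored water, where the Background raises recontamination during collection, storage and handling.

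**What to change.** - Keep the zero proportion, defined separately for each test and organism. Zero E. coli remains a sensible endpoint.
- Add one prespecified GEE comparison per organism: either log10(count+1), reported as a ratio of geometric means of count+1, or ordered categories such as <1, 1–9, 10–99 and ≥100 CFU/100 ml. The categories should include the 10 CFU line. The protocol states that line for thermotolerant coliforms, so its use for another organism should be declared.
- State the volume filtered, the rule for non-detects and the value used for counts above the upper limit.
- Report H2S as positive in 20 ml, not as absence or presence of contamination in general.

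No new data are needed. The cost is a little more analysis and one more secondary comparison per organism.

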## Ethical Assurance for Protection of Human Rights

Describe the justifications for conducting this research in human participants. If the study needs observations on sick individuals, provide sufficient reasons for using them. Indicate how participants rights will be protected, and if there would be benefit or risk to each participants of the study.

This study enrols human subjects, because the study question addresses the issue of the impact of additional water treatment behavior on human health and the question can only be answered by enrolling human subjects. The objectives and study procedures will be explained to all candidate households and only households that provide informed consent will be enrolled. Households will be free to drop out of the study at any time.

Benefits to the study participants include that some participating families will receive water treatment and/or a water storage container. Moreover, if the study shows that treating tubewell water at the household level and storing it safely is effective in improving children’s health, the safe storage group and the non-intervention group will be given a six-month supply of chlorine tablets at the end of the study and the non-intervention group will also be given a safe storage container such that all study participants will ultimately have received water treatment tablets in addition to safe storage containers. At the end of providing free tablets, all three study groups will also be encouraged to continue to treat their water. If children are identified through the routine surveillance who appear seriously ill to do field research assistant, they will be referred to an appropriate healthcare facility.

If the participants consent to participate in the five additional follow-up and promotional visits, we will provide these intervention container and tablets to the control arm households after these additional visits. However, during reconsenting, we would provide all the participants color pencils/toys for their small kids. This would be a token of appreciation but not compensation, which will help for the intellectual development of their kids but has small monetary value.

The risks to study participants are few. Chlorine treatment of drinking water has been used for over a century and is widely recognized as a safe and appropriate way to treat drinking water. The specific chemical used for water treatment in this study, sodium dichloroisocyanurate, has been reviewed by the World Health Organization and judged to be safe (Clasen and Edmondson, 2006).

The control group will receive no water treatment during the study period, but will continue to be followed while they use their standard water collection habits and storage practices. This group risks being exposed to significant waterborne pathogens without treatment. If, over the course of the study, we encounter households in this group whose drinking water does not meet the WHO criteria for low risk (less than 10 CFU of thermotolerant coliforms per 100 mL), these households will be notified of their water quality results, informed about locally available water treatment methods and encouraged to use them. These include liquid bleach, bleaching powder and halotablets, as well as boiling. Moreover, this group is not being exposed to any increased risk by participating in the study. Indeed, their water collection and storage practices are the standard practices of tens of millions of Bangladesh households every day. We do not know if this low-level exposure to fecally contaminated drinking water leads to significant household diarrhea. Many commentators argue that low levels of contamination are not a significant health risk (Moe et al., 1991). The only way that we can learn whether increased efforts to improve the microbiological quality of drinking water will reduce diarrhea is by evaluating the intervention. This evaluation requires a non-intervention group for comparison.

## Use of Animals

Describe if and the type and species of animals to be used in the study. Justify with reasons the use of particular animal species in the experiment and the compliance of the animal ethical guidelines for conducting the proposed procedures.

Not applicable

## Minor changes made to this protocol before study implementation:

1. Random subset of households in randomly selected villages (instead of systematic subset of households in villages close to the field office) to achieve representative random sample.
2. 180 households (60 from each study arm) tested for *E. coli* and total coliforms instead of 150 households (50 from each study arm) to achieve testing in 10% of study households.
3. MI Agar (Becton, Dickinson and Company, Maryland, USA) to enumerate *E. coli* and total coliforms instead of MI Broth (Whatman Inc, New Jersey, USA).
4. Digital colorimeter (Hach, Colorado, USA) to measure free chlorine residual instead of DelAgua kit to achieve increased precision.
5. Longitudinal prevalence in the protocol used to refer to period prevalence. Period prevalence measured to avoid inaccuracies associated with collecting diarrhea data for each day of the 7-day recall period.

